Following the visit with their provider, patients will complete the post-visit surveys that assess the proposed mediator variables, including 1) a standardized measure of patient activation, 2) a measure of attitude, perceived social norms, perceived behavioral control, 3) a measure of anticipated emotion regarding managing their blood pressure, and 4) a visit satisfaction survey. Patients will receive a \$20 gift card in compensation for participation. Participants must complete the values affirmation exercise in order to receive compensation for participation. Where patients are not able to complete all other surveys at the baseline/index visit, they will have the option of being contacted by study coordinators via phone to complete any remaining surveys, or to complete surveys via a direct web link to REDCap, that can be sent to them via email.

At 3-months, subjects will be called by the research assistant to schedule 3-month visit which includes measures of blood pressure, pill counts, self-reported adherence survey and the proposed mediators of the intervention effect (Table 1). This visit may coincide with a regularly scheduled follow-up visit with their provider. At 6-months, all subjects will return for an in-person visit to have their blood pressure measured by the research assistant and complete a 6-month survey with the same measures as those obtained at 3-months (Table 1). This visit may also coincide with a regularly scheduled follow-up visit with their provider. At the 3- and 6-month visits, patients will also be asked to bring all antihypertensive medications for pill count assessment, and will receive an additional \$20 gift card as compensation for participation. If patients are unable to attend either the 3 or 6-month follow up in person visit, they will be given the option to complete the surveys over the phone, or to complete surveys via a direct web link to REDCap that can be sent to them via email, and their incentive will be mailed to their home.

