**Attitudes Survey.** In order to explore other potential mediators of the relationships between values affirmation, improved patient-provider communication and improved patient intention for self-care, we rely on constructs from the Theory of Planned Behavior as modified by Perugini and Bagozzi and tested in patients with hypertension. The Theory of Planned Behavior posits behavior intention as the most proximal predictor of behavior, and that intention is influenced by the individual's attitude towards the behavior, by the social norms surrounding the behavior, and by the individual's perceived control over the behavior. Taylor and Bagozzi modified this theory by adding the concept of desire for the behavior and its consequences, which in turn is influenced by the anticipated positive and negative emotions associated with the behavior. We have adopted the questions from this study to assess attitudes, norms, perceived control, and emotions around blood pressure management. (see Attitudes Survey) We will add an additional question to include physicians' opinions in the patients' perception of social norms: "I care what my doctor thinks about my efforts to control my blood pressure", with responses ranging from "not at all" to "very much" along a 5-point scale.

**Patient assessment of visit** – As in our pilot study, as a secondary outcome, we will use the Barr's 4-item provider specific modification of the Medical Outcomes

Study Visit Satisfaction Questionnaire, which is sensitive to differences in patient satisfaction by race.

**Provider Measures.** – We will assess provider factors that may moderate the relationship of the intervention with adherence including implicit racial bias, prior cultural awareness training, self-efficacy regarding caring for African American patients and interracial mix of clinical site. These measures will be included in a web-based survey and were chosen based on literature suggesting these factors influence the quality of the patient-provider interaction and were associated with differences in racial attitudes among health care providers. This survey will be completed by providers at their convenience and independent of the patient index visit. (see Provider Survey)

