#### **F. Data Analysis Plan:**

**Sample size estimation.** For our primary analysis, we assume a three-level model, with patients nested within providers and providers nested within clinics. Assuming comparable variation in adherence and  $\alpha=0.05$ , a sample size of 960 subjects (240 each cell in values affirmation, or control; 480 African American, 480 white) will be required to detect an effect size of 0.26 difference in adherence between any two cells with a power of 80%. Based on the pilot study results, a 0.26 effect size is approximately a 4.7% absolute difference in adherence scores. Since randomization is at the patient level, the intraclass correlation coefficient for patients nested within clinicians will

have a negligible effect on power. We conservatively estimate an attrition rate (neither having a med refill within the system nor returning for follow up) over all sites of 15%. We therefore will enroll an additional 170 patients to compensate for this attrition, for a final sample size of 1,130. We will cap enrollment at 450 subjects per site to ensure generalizability of results.

For moderation hypotheses, the primary contrast of interest is the adherence difference between African Americans with high and low past experiences of discrimination (dichotomized scores for ease of interpretation) who receive the intervention. Using a median split on the discrimination scores, the sample size for this comparison would be 120 in each subgroup. This sample size will provide >80% power to detect a 0.37 SD difference in adherence. For the patient activation mediation analyses, a sample size of 480 (e.g. African Americans only) will provide >80% power to detect a 0.13 partial correlation between change in the patient activation and change in adherence, adjusting for other variables in the model; a sample size of 960 will provide >80% power to detect a .10 partial correlation. Parchman et al report a standardized regression coefficient of 0.16 between patient activation and the Morisky medication adherence scale. While our proposed analytic approaches differ, this gives some indication of the anticipated strength of the relationship.

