The primary outcome variable (adherence measured by pharmacy refills) is continuous; in the event that normality assumptions are not met we will use transformations to normalize distributions. For the primary comparisons, we will employ intent-to-treat analyses, although we expect few or none of the randomized patients to not complete an exercise. We will examine overall values affirmation effectiveness between the racial groups. We will next create models with adherence as the dependent variable including the potential moderator variable (prior experience of discrimination) then including the potential mediator variables (patient activation, attitude, social norms, perceived behavioral control, and anticipated emotion). Finally, we will explore whether the collected provider variables (racial bias, past cultural competency training, self-efficacy and racial mix of clinical site) moderate the relationships. We will also include patient gender and provider race as a possible moderating variables. We will use general (or generalized, for dichotomous outcomes) linear mixed models, examining alternative structures for the variance-covariance matrix for the level 1 model by comparing goodness of fit for the different models as well as model fitting diagnostics to assess for influential points, outliers, overdispersion and heteroscedasticity. We will employ methods that utilize all available data, assuming ignorable missingness.

In secondary analysis using the self-reported adherence measures, we will dichotomize the groups into non-adherent (score  $\geq 2$  on any "extent" item) and adherent. We will also compare the pill count measure of adherence to the pharmacy fill estimates of adherence for validation. For blood pressure, the secondary outcome, we will compare the index and follow-up visits using mixed effects repeated measures models with a patient random effect. All hypothesis tests will be two-sided with  $\alpha=.05$ . Statistical analysis will use SAS 9.4.

**Statistical Model for Primary Outcomes.** The structure of the data is hierarchical (patients nested within providers) and longitudinal (repeated measures on patients over time). Baseline (time 0) is defined as the adherence rate for the 12-months prior to the index visit.

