where  $\gamma_{000}$  is the intercept in the provider level model for  $\beta_{00j}$  (i.e. initial status for white controls);  $\gamma_{010}$ ,  $\gamma_{020}$ , and  $\gamma_{030}$  represent overall baseline differences by intervention status and race.  $\gamma_{100}$  is the linear growth rate for white controls;  $\gamma_{110}$ ,  $\gamma_{120}$ , and  $\gamma_{130}$  represent differences in slope by intervention status, race, and both.  $u_{00j}$  is a provider random effect. Thus, hypotheses can be tested directly by examining coefficients for the terms above or by means of linear contrasts.

Mediator analyses for the adherence outcome will use methods that completely partition between and within patient effects, with *change in adherence* as the primary outcome and *change in PAM scores* (or other measure) as the primary independent variable.

In addition to the planned analyses above, several additional analyses will be conducted using the study's currently collected data. No new data or variables will be collected. The results of the analyses will be included in abstracts for meetings/conferences, and/or in manuscripts submitted for publication. The list of additional analyses are below:

1. **Social vulnerabilities to disparities and participant attrition:** To explore whether social vulnerabilities are associated with participant attrition in a randomized trial, we will examine the relationship between age, minority race-ethnicity, sex, financial strain, insurance status, unemployment and educational attainment with enrollee attrition over 6 months.
2. **Racial differences in theory-based constructs related to hypertension management:** To understand the extent to which attitudinal constructs predict adherence behavior across racial groups, we will estimate a model in which prior adherence is the primary variable that predicts current attitudes towards adherence, norms supporting adherence, and perceived

- behavioral control over adherence. Perceived discrimination will be explored as an additional predictive measure. Future analyses may be similar to those listed above but will instead examine the value of attitudes, norms, and perceived behavioral control in predicting medication adherence for each of the racial groups at 3- and 6-month follow-up.

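### Additional analysis 2 sets out to learn how far attitudes predict adherence by race, but the model it commits to has prior adherence predicting attitudes

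*Protocol*

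**What the plan says.** Section F of the Protocol ends with six additional analyses whose results are to go into abstracts or manuscripts. The second concerns racial differences in theory-based constructs.

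- **Purpose:** "To understand the extent to which attitudinal constructs predict adherence behavior across racial groups".
- **Model committed to, in the same sentence:** "we will estimate a model in which prior adherence is the primary variable that predicts current attitudes towards adherence". Norms and perceived behavioral control are further outcomes of that model.
- **Later work:** "Future analyses may be similar to those listed above but will instead examine the value of attitudes, norms, and perceived behavioral control" as predictors of adherence in each racial group at the 3- and 6-month follow-up.

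Three other places fix the timing and direction of these variables.

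- **Prior adherence** (section F, statistical model for primary outcomes): "Baseline (time 0) is defined as the adherence rate for the 12-months prior to the index visit". The outcome section (IV.A) uses the same 12-month window for prior adherence.
- **Attitudes** (section B, patient recruitment and procedures): after seeing the provider, "patients will complete the post-visit surveys that assess the proposed mediator variables". Table 1 likewise puts the attitudes survey in the post-visit column and again at 3 and 6 months.
- **Theory** (section C, Attitudes Survey): "intention is influenced by the individual's attitude towards the behavior, by the social norms surrounding the behavior", and intention is the closest predictor of behavior.

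**The concern.** Predictor and outcome are swapped between the purpose and the model. The model's null hypothesis is that past adherence is unrelated to present attitudes. The question asked has a different null: that attitudes do not predict adherence. The two hypotheses can be true or false independently of each other.

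At stake is what an abstract or manuscript from this analysis could claim. Under the stated purpose, a significant coefficient invites the reading that attitudes predict adherence, and a coefficient that differs by race invites the reading that different things predict adherence in the two groups. The committed model supports neither. The model that could is left optional.

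**Working it through.** **No figure to reproduce.** The Protocol gives no effect size, sample size or power for this analysis. The check is therefore a reading of the text, followed by an illustration on assumed correlations.

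**Direction, side by side**

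| | Predictor | Outcome | Status |
|---|---|---|---|
| Stated purpose | attitudes, norms, control | adherence | the question |
| Committed model | adherence, 12 months before index visit | attitudes, norms, control after index visit | will be done |
| Follow-up model | attitudes, norms, control | adherence at 3 and 6 months | may be done |

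The committed model cannot be read in the direction of the purpose, because the attitudes are collected after the adherence window has closed.

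**The two coefficients are separate quantities.** In standardised variables, let P be prior adherence, T a post-visit attitude score and L later adherence.

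- Written model (T on P): slope = r(P,T).
- Forward model (L on T, adjusted for P): slope = [r(T,L) − r(P,T)·r(P,L)] / [1 − r(P,T)²].

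If T adds nothing beyond P, then r(T,L) = r(P,T)·r(P,L). The forward slope is then zero whatever r(P,T) is. With r(P,T) = 0.16 and r(P,L) = 0.6:

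- r(T,L) = 0.16 × 0.6 = 0.096
- forward slope = (0.096 − 0.096)/(1 − 0.0256) = 0
- written slope = 0.16

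**Inputs for the illustration.** From section F: 480 analysable patients per racial group, 960 in all, and two-sided alpha 0.05. Assumed: r(P,T) from 0.10 to 0.50 and r(P,L) from 0 to 0.6. The value 0.16 is the standardised coefficient that section F quotes for patient activation and adherence. It is borrowed only for scale, since it does not concern these constructs.

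**Case 1: attitudes add nothing beyond prior adherence.** Chance that the written model is significant, by Fisher's z: Φ(atanh(r)·√(n−3) − 1.96).

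| r(P,T) | n = 480 | n = 960 |
|---|---|---|
| 0.10 | Φ(2.19 − 1.96) = 59% | Φ(3.10 − 1.96) = 87% |
| 0.16 | Φ(3.52 − 1.96) = 94% | Φ(4.99 − 1.96) = 99.9% |
| 0.20 | Φ(4.43 − 1.96) = 99% | about 100% |

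A simulation of this case used r(P,T) = 0.16, 0.3 and 0.5, r(P,L) = 0, 0.3 and 0.6, both sample sizes, and 600 runs for each of the 18 settings. The written model was significant in 93–95% of runs at n = 480 with r(P,T) = 0.16, and in 100% elsewhere. The forward model adjusted for prior adherence was significant in 3.5–6.0%, against a nominal 5%.

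**Case 2: attitudes do add to later adherence but are unrelated to prior adherence.** Section F uses a partial correlation of 0.13 at n = 480 for patient activation. The same value here gives the forward model Φ(atanh(0.13)·√477 − 1.96) = Φ(2.86 − 1.96) = 81% power. The written model has r(P,T) = 0, so it is significant about 5% of the time.

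**Case 3: comparison by race.** Suppose r(P,T) is 0.30 in one group and 0.10 in the other (assumed), with 480 in each, and attitudes add nothing beyond prior adherence in either.

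- z = (atanh 0.30 − atanh 0.10)/√(2/477) = (0.3095 − 0.1003)/0.0648 = 3.23
- chance of a significant racial difference = Φ(3.23 − 1.96) = 90%
- true race difference in the forward slope = 0

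**Why the forward model needs prior adherence.** In the same 18 settings the forward model without that adjustment stayed at about 4–5% when r(P,L) = 0. It rose to 18–100% when r(P,L) was 0.3 or 0.6, because T then stands in for P.

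**The case against.** **The forward direction is already planned elsewhere.** This largely stands. Section F commits to models with adherence as the dependent variable that bring in attitude, norms, perceived control and anticipated emotion as mediators. It also commits to mediator analyses with change in adherence as the outcome. These are correctly oriented, so a reader who infers that the Protocol never examines whether attitudes predict adherence would be wrong. They are not, however, described as comparing that prediction between racial groups, which is what additional analysis 2 promises.

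**The direction is disclosed.** The item's title suits constructs as outcomes, the text says plainly what predicts what, and the model respects time order. It may be a two-step plan with one loose purpose clause. That is a fair reading, and it is why the point is minor. The clause still sets a question that the committed step does not address.

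**The percentages only restate the assumptions.** Correct. The 59–99% range at n = 480 is power to detect an association assumed to exist. It is not a false-positive rate of the written model, which is a valid test of its own hypothesis. The figures show only that the two questions can have opposite answers.

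**Attitudes may still predict later adherence without adjustment.** Also correct. A reader might infer that the written model can be positive when attitudes predict nothing at all. Case 1 does not show that in general. Its null is nothing beyond prior adherence, and when adherence persists over time attitudes correlate with later adherence in their own right.

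**No treatment-arm term is mentioned.** It is tempting to add this as a fault, because the survey follows the randomised exercise. The documents do not support it: covariates may be left to the analysis plan, and arm is randomised, so omitting it does not bias the slope on prior adherence.

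**Conclusion.** Wrong as written, and minor. The purpose and the committed model of additional analysis 2 contradict each other, and the race-specific model that fits the purpose is optional. This conclusion rests on the text and needs no assumption. The numerical illustration rests on assumed correlations and on the Protocol's target of 480 and 960 analysable patients. Under those, the committed model can be positive in most studies when attitudes add nothing beyond prior adherence, and positive in only about 5% when they do add something.

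The consequence is confined to one exploratory analysis with no stated hypothesis or decision rule. A reader might infer that the mediation plan or the main results are compromised. They are not: the mediator models are correctly oriented, and Aims 1 to 3, the primary outcome and the sample size do not depend on this analysis.

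**What to change.** 1. Make the follow-up model the planned analysis for the stated purpose. The outcome is adherence at 3 and 6 months. The predictors are post-visit attitudes, norms and perceived control, adjusted for prior 12-month adherence and arm, with race-by-construct terms to compare the groups.
2. Keep the present model under a purpose that it can serve: whether prior adherence is associated with current attitudes, norms and perceived control, by race.

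If only the present model is wanted, correcting the purpose clause alone removes the contradiction, but the question of what predicts adherence by race then goes unanswered.

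The cost is a few sentences of rewording. Every variable is already collected, and the follow-up model is already named as a possibility.

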a PCP. Potential participants will be told the research is being done to assess adherence to hypertensive medications and to evaluate how a writing exercise about values might affect blood pressure. If they express interest in the study, they will be asked to arrive approximately one hour prior to the visit in order to review study procedures and provide informed consent. (see Patient Informed Consent) Those who decide to participate will have their blood pressure measured by the research coordinator using guideline-recommended procedures. Next, participants will be given a pre-randomized, consecutively numbered packet – to ensure the research coordinator is blind to the condition - containing the study materials. Packets will contain either an intervention or control version of the values affirmation exercise. To ensure balanced randomization by race at each site, there will be a pre-randomized series of packets for participants who self-identify as white and another pre-randomized series for those who self-identify as African American. Additional surveys will include a baseline demographics questionnaire, a measure of past experiences of discrimination, and a self-reported adherence (Voils) measure. (Table 1) Where patients feel comfortable using a tablet device, surveys will be administered and data will be collected on the tablet via an online survey format and stored in REDCap. If they do not feel comfortable with this format, all surveys will be administered on paper only. The values affirmation exercise will always be administered on paper, and the research assistant will provide instruction and remain available, but the patient will complete the exercise on their own, at their own pace. In our pilot work, patients completed all study materials in ~30 minutes. Next, patients will undergo routine check-in procedures, which includes blood pressure measurement at all sites, and complete the scheduled visit with their provider.

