3. Racial differences in values and qualitative themes: We will use quantitative Poisson regression models and qualitative content analysis to determine the frequency of values chosen during the values affirmation writing exercise and identify common qualitative themes for why each value was chosen among racial groups.
  4. Past experiences of discrimination and uncontrolled blood pressure: We will determine whether there is an association between past experiences of discrimination and the degree of uncontrolled blood pressure at patients' index visit. If so, we will examine potential moderators of that relationship (satisfaction with clinician, patient activation, attitudes toward blood pressure control) while controlling for socioeconomic status and treatment variables.
  5. Pill management strategies and pill count adherence: To investigate how strategies used by patients to manage their medications outside the clinic are associated with adherence to medications, we will describe the self-reported frequency of strategies used by patients to manage their pills at home. The association between each strategy and patients' pill count adherence (proportion of actual over expected pills taken) will be determined at each study timepoint. In secondary analyses, the strategies associated with apparent outliers will be examined at the baseline visit.
  6. Factors contributing to the racial disparity in antihypertensive medication adherence: To assess whether racial disparities in medication adherence can be explained by pre-specified covariates, we will use the Oaxaca-Blinder decomposition method. We will determine general sample characteristics of the patient population who are adherent and non-adherent to antihypertensive medications, determine the overall disparity in medication adherence between White and Black patients explained by covariates, and then calculate the contribution each covariate to the disparity in medication adherence by race. Pre-specified covariates will include those already collected during the study (demographics, clinical factors, medication use, health care utilization, perceived discrimination, attitudinal factors, and behavioral factors). **UCD will share a de-identified data set with one of our subcontractors (Kaiser Permanente Mid-Atlantic States), and they will conduct these analyses on site.**

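### Additional analysis 4 treats scores first collected after the index blood pressure, the exercise and the visit as moderators of that blood pressure, and tests them only if an average association is found

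*Protocol*

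**What the plan says.** Section IV.F of the protocol ends with six additional analyses of data already being collected. Item 4 sets the question: "We will determine whether there is an association between past experiences of discrimination and the degree of uncontrolled blood pressure at patients' index visit". The next sentence makes the follow-up conditional and lists the variables: "If so, we will examine potential moderators of that relationship (satisfaction with clinician, patient activation, attitudes toward blood pressure control". The adjustment is stated as "while controlling for socioeconomic status and treatment variables"; whether randomised arm counts as a treatment variable is not said.

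The order of events at the index visit is in section IV.B, under patient recruitment and procedures:

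1. Research BP: "Those who decide to participate will have their blood pressure measured by the research coordinator using guideline-recommended procedures".
2. Randomised exercise: "Next, participants will be given a pre-randomized, consecutively numbered packet".
3. A second BP at check-in: "patients will undergo routine check-in procedures, which includes blood pressure measurement at all sites".
4. The consultation.
5. The three scores: "Following the visit with their provider, patients will complete the post-visit surveys that assess the proposed mediator variables". The list that follows includes activation, attitudes and visit satisfaction.

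Table 1 in section IV.C agrees. The pre-visit survey holds only prior discrimination and self-reported adherence. Activation, attitudes and the impression of the visit are post-visit, and the first two are repeated at 3 and 6 months.

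**The concern.** A moderator is normally something in place before the outcome it modifies. Here the outcome comes first. By the time the scores are taken, the patient has had two BP readings, has done one of two randomised writing tasks and has seen the provider. A high reading may lower activation, colour attitudes or shape satisfaction with the visit. The protocol itself classes activation and attitudes as mediators, that is, as things the exercise should change, and hypothesis H2 expects the effect of the exercise to vary with past discrimination.

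Two things follow. If a score depends on BP, putting it in the model changes what the discrimination coefficient means, and the interaction term can pick up the shape of the BP-to-score relation instead of any modification of BP. Separately, requiring an average association first screens out the pattern that moderation analysis is meant to find, where the association is present in some patients and absent or reversed in others. The results are intended for abstracts and manuscripts, so a published statement that activation or satisfaction moderates the link between discrimination and BP could partly be reverse causation.

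**Working it through.** **Inputs from the protocol.** Enrolled sample 1,130; two-sided alpha 0.05; visit order as above. Item 4 has no sample size, power or effect size of its own, so there is no stated figure to reproduce for it. The trial sample size it borrows does reproduce: 960 / 0.85 = 1,129.4, rounded to 1,130. All effect sizes below are assumptions in SD units.

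**1. Timing.** The pre-packet research BP and the check-in BP both precede the post-visit survey, so the order problem holds whichever reading is used. Item 4 does not say which one is. The distinction still matters, because only the first reading is free of the exercise. Table 3 labels the first activation and attitude measurements as baseline, but Table 1 and the text on patient activation place them after the index visit.

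**2. Discrimination slope, linear case.** Let BP = 0.15 D + e, with Var(e) = 1 − 0.15² = 0.9775. Let the score be M = −a BP − 0.3 D + u, with Var(u) = 1. There is no true moderation. The coefficient of D once M is in the model is

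0.15 − a × 0.9775 × (0.15a + 0.3) / (0.9775a² + 1).

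- a = 0.10: 0.15 − 0.0305 = 0.120
- a = 0.16: 0.15 − 0.0494 = 0.101
- a = 0.30: 0.15 − 0.0930 = 0.057
- a = 0.50: 0.15 − 0.1473 = 0.003

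With a = 0 the slope stays at 0.15. If discrimination has no direct effect on the score (0.3 replaced by 0), a = 0.30 gives 0.138, so most of the attenuation needs both paths. The direction depends on the assumed signs.

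**3. False interactions.** Simulation at n = 1,130, 2,000 datasets per setting, robust standard errors, arm adjusted, same model, no true moderation:

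| BP effect on score (a) | Linear score | 40% of patients at the top of the scale | Slope with that ceiling |
|---|---|---|---|
| 0 | about 5% | about 5% | 0.15 |
| 0.10 | 5–6% | about 7% | about 0.12–0.13 |
| 0.16 | 5–6% | about 9–10% | 0.11 |
| 0.30 | 5–6% | about 15–17% | about 0.076 |
| 0.50 | about 6% | about 34–35% | about 0.033 |

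Splitting the score 70/30 instead gives about 7–11%. In a separate set of runs at n = 960 (true slope 0.2), a BP effect on the score that itself varies with discrimination by 0.05, 0.10 or 0.20 gives false interactions in 19%, 58% and 99%. An effect of the exercise on the score that varies with discrimination gave only 5–6%, with or without adjustment for arm.

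**4. The condition.** Take a slope of 0.12 in one half of patients and 0 in the other, n = 1,130.

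- Average slope 0.06: z = 0.06 × √1130 = 2.02
- Interaction 0.12: z = 0.12 × √1130 / 2 = 2.02
- Power of each: Φ(2.02 − 1.96) ≈ 0.523
- Both, the two estimates being uncorrelated in an even split: 0.523 × 0.523 = 0.27

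Detection falls from 52% to 27%. In the extreme case of a zero average association with a true interaction of 0.10–0.20 (n = 960), the unconditional test has 84–100% power, and the conditional procedure finds moderation in about 5%.

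**The case against.** The strongest reply is that time of measurement is not time of existence. Activation and attitudes are lasting dispositions, and a survey an hour later may stand in for their earlier values. Item 4 is exploratory, speaks of potential moderators and claims no causal effect. This stands in part: the documents do not support saying that the scores could not have modified BP, only that they may be contaminated by it, by the exercise or by the visit. The contamination is most direct for visit satisfaction.

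A reader might also infer that post-outcome measurement produces spurious moderation as a matter of course. It does not. Under linear dependence the false-positive rate stays near 5%. The larger rates need a ceiling or a nonlinear response, and the highest ceiling figures also need a BP effect of 0.3–0.5 SD on the score; the protocol gives neither. The instruments are built from Likert-type items, so a ceiling is plausible but not documented.

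On the condition, following up moderators only once an association is seen is a common way to limit testing. Item 4 names no significance threshold; that reading is inferred from the two-sided 0.05 rule that section IV.F applies to all hypothesis tests. The 52% to 27% drop is one chosen case. Even so, an average association is the wrong prerequisite for a question about heterogeneity.

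**Conclusion.** The point holds in a limited form. The time order is clear from the protocol's own visit sequence, and both the choice of moderators and the condition are stated rules, not details left to a later plan. Conditioning on the scores can attenuate the discrimination slope when they depend on BP, from 0.15 to between 0.12 and near zero under the assumed effects of 0.10–0.50 SD. False interactions are conditional on a bounded or nonlinear score, or on a BP response that differs by discrimination. The condition can roughly halve detection of a partial slope and removes it almost entirely when opposing slopes cancel.

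It would be tempting to conclude that the trial's main findings are at risk. They are not: this is one of six additional analyses, with no bearing on the primary or secondary outcomes, the randomised comparison or the sample size. Importance is low to moderate.

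**What to change.** Reword item 4 of the additional analyses in section IV.F:

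- Delete the opening condition and test the three interactions whatever the average association shows.
- Name the research BP taken before the packet is handed out as the outcome.
- Include randomised arm in the adjustment set. This deals with the exercise but not with any effect of BP on the scores.
- Report the discrimination–BP slope from the model without the post-visit scores.
- Describe the interactions as exploratory associations with post-visit scores, not as moderation of index BP.

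A model with 3- and 6-month BP as outcome may be added as a sensitivity analysis, since those readings follow the scores. It should not replace the main analysis. Past discrimination precedes both readings, so adjusting for index BP changes the question. In simulation (true interaction 0.10, 15% loss, stable share of BP variance 0.5–0.7) it cut power from about 93% to roughly 26–48%.

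No new data are needed, which matters because the protocol rules out collecting any for these analyses. The cost is a few more exploratory tests.
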